### Data Collection

#### Variables

Variables for analysis were selected conceptually based on the Andersen behavioral model of health services use, a well-established model that provides a context for characterizing the many factors which lead to health care use [26-29]. Within this model, both contextual and individual factors influence patients’ initial ED visits and downstream health care use and outcomes. This model has been used to frame numerous prior studies involving ED use and falls among older adults [30,31], as well as the initial design and validation study of this intervention. During previous work, we have built a rich data set of covariates with over 700 potential EHR data features at ED 1 and will add data from ED 2 and ED 3 using the same data definitions [20]. These include patient factors, such as age, sex, race, ethnicity, and previous health system use; enabling factors, such as financial and physical availability of care; and ED encounter level factors, such as treatment team composition, ED length of stay, reason for visit, emergency severity index, diagnostic tests, and pharmaceutical and therapeutic interventions.

#### Data Retrieval Process

Data will be collected from the EHR in 4 steps. First, we will retrieve data about the patient, their index ED visit, and falls risk information—ML algorithm risk score, walking aids, history of falls, and acute care usage—from the EHR. Second, these data and information about referral orders and subsequent scheduled visits with the mobility and falls clinic will be uploaded to a Health Insurance Portability and Accountability Act (HIPAA)-compliant database built in a Research Electronic Data Capture (REDCap; Vanderbilt University) database [32]. This REDCap database is needed so documentation about the reason a patient did not ultimately schedule or attend the clinic visit can be abstracted. Specific reasons for not completing the referral are not always documented discretely, so they will be abstracted from free-text scheduler notes by 2 trained reviewers. Specifically, the reviewers will look for reasons the patient was documented to be ineligible. Reasons include whether the patient is in other physical therapy, in hospice, or in memory care; is too advanced to benefit, immobile, or wheelchair-bound; and whether the patient or caregiver declined or was unreachable. Third, after verifying outcome variables and the reason for not scheduling a visit, the data on the clinic visit will be joined with the curated data described above into a limited data set for analysis. Finally, falls outcome data will be merged with Medicare claims data to determine if the patient was treated for a fall at an outside ED.

### Statistical Analyses

#### Primary Outcome: Completed Referrals

The primary association of interest is whether an ED-based referral from an ML-based CDS can successfully cause patients to complete a specialist appointment. To assess the effectiveness of our program for patients receiving the falls risk intervention, our primary analysis will be to obtain point estimates and the 95% Wald CI of referral completion rate by site. We will perform a similar analysis to identify rates for prespecified process metrics, including referral orders placed among flagged patients and clinic appointments scheduled among at-risk patients. Further, we will perform a secondary analysis to identify subgroups at risk for lower odds of referral completion using a logistic regression model for each site to predict referral completion as a function of demography (sex, age, race, ethnicity, and education) and fall risk score. A model built for each site will account for site-level variability. Estimated coefficients and their 95% CIs will indicate risk factors for poor referral completion. This will help inform future implementation by, for example, identifying risk score thresholds for obtaining target rates of completed referrals for a given patient population.

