### Outcomes

Our primary outcome is the rate of completed referrals to the Mobility and Falls Clinic among patients identified as high-risk. We define a completed referral as a patient completing an initial visit with a falls prevention specialist at the mobility and falls clinic.

Our secondary outcome is return visits to any ED for a fall within 6 months of the index ED visit, the outcome our ML algorithm was trained to predict. This outcome is meant to reflect the overall effectiveness of the intervention in preventing falls among patients identified as high-risk.

Additional process outcomes will be investigated to deconstruct steps from the identification of high-risk patients to completed referrals. These include whether a patient was referred to the outpatient mobility and falls clinic after being identified as high risk, whether referred patients were reached by schedulers, and whether referred patients scheduled an initial appointment, regardless of whether they attended.

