#### Statistical Power

With the plan to flag 5 patients per week at each referral site, we plan to refer 520 patients per site, generating 1560 total patients referred. A sample size of 520 would lead to 95% Wald CI for referral completion rate by site that is 8.6% in width or smaller. This width provides sufficient precision for our study, considering that (1) a completion rate as small as 10% would be clinically meaningful and (2) we expect to observe a referral completion rate of 50% or higher—in which case, there would be nearly 100% power to reject a referral completion rate of 10% at a significance level of .05 when n=520.

For reference, very few patients were referred from the ED to the mobility and falls clinic prior to our intervention, and the clinic estimates that 80% of their patients referred from other providers visit the clinic. Power can be estimated for detecting a significant intervention effect on fall risk, provided additional covariates are ignored. In this case, a score test for this effect is equivalent to a Cochran-Mantel-Haenszel test of independence in a stratified sample. Such a test has 89.7% power to detect a difference in fall risk of 10% in a stratified sample size of 12 groups (in twelve 8-week periods over 2 years) assuming (1) a significance level of .05, (2) 40 patients receive the intervention and 40 patients do not who have similar risk scores, and (3) an average fall risk of 25%. For reference, our preliminary work predicted a number to treat of about 10 (ie, a fall risk difference of 10%) when setting the risk score threshold so that 5 persons per week receive the intervention (or 40 persons per 8 weeks) and an average fall risk of about 25% for individuals with a fall risk score above or near the fall risk score threshold. We plan on exploratory analysis of pooled data to evaluate the effect of specific covariates on rates of referral; in these cases, power will be lower based on the incidence of specific covariates in the data.

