### Significance of Principal Findings

Previous work with ML-CDS tools has focused on their implementation in a specific context [33] or on the predictive performance [34] of the underlying algorithm. Our unique data set will include information about patient’s health history (eg, health care use) prior to the ED index visit, referral completion, and subsequent ED return visits for falls (either in the system or from Medicare claims), providing a more complete picture of a given patient’s trajectory than most studies. We will use this unique data set to track not just ML-CDS performance in the context of its implementation, but in the context of larger patient health outcomes, which, to our knowledge, has not been done for this kind of long-term, preventative ML-CDS system. Similarly, the multisite implementation plan will demonstrate applicability to a broad population and the possibility to adapt the intervention to other EDs and achieve similar results.

Our statistical methodology (a regression discontinuity design) allows for an intent-to-treat causal inference about the impact flagging high-risk patients can have on patients’ future falls. Conversations with patients about the referral, even if a referral is not written, could have impacts on patients’ risk awareness and compliance with physical therapy, so ML-CDS flagging is the correct epidemiologic exposure to assess with respect to the outcomes of completed mobility and falls visits or return ED visits for falls. A staggered implementation strategy allows for the identification of secular trends that could affect causal association and mitigation as necessary.

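### The primary question is causal, but the primary analysis is a one-group completion rate; the threshold comparison that could address it is planned only for falls

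*Protocol article*

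**What the plan says.** The section Primary Outcome: Completed Referrals opens with the aim: "The primary association of interest is whether an ED-based referral from an ML-based CDS can successfully cause patients to complete a specialist appointment". It then fixes the analysis: "our primary analysis will be to obtain point estimates and the 95% Wald CI of referral completion rate by site". The Outcomes section limits the measure to flagged patients: "Our primary outcome is the rate of completed referrals to the Mobility and Falls Clinic among patients identified as high-risk".

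Statistical Power supports this with precision and a fixed benchmark. On precision: "A sample size of 520 would lead to 95% Wald CI for referral completion rate by site that is 8.6% in width or smaller". On the benchmark, it says that "a completion rate as small as 10% would be clinically meaningful" and that "we expect to observe a referral completion rate of 50% or higher", which gives near-certain rejection of 10% "at a significance level of .05 when n=520".

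The comparison of flagged patients with unflagged patients of similar risk appears under Secondary Outcome: Return Visits to ED for a Fall, for that outcome only. The other models that involve completion (a logistic model by site and a stratified Cox model) examine covariates, not flagged against unflagged patients. Yet Significance of Principal Findings says that "ML-CDS flagging is the correct epidemiologic exposure to assess with respect to the outcomes of completed mobility and falls visits", alongside falls.

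**The concern.** A completion rate among flagged or referred patients has no counterfactual. It shows how many attended, not how many attended because of the tool. Every study patient has a primary care provider in the same health system, and the clinic receives referrals from other providers, so a flagged patient could reach it by another route. Such a visit would count as a success, and neither the rate nor its interval would show it.

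At stake is the wording of the main conclusion. The Discussion expects to show a beneficial impact of automated screening on completed referrals as well as on falls. The first half of that claim has no planned analysis that could support it, although the article already describes the design that would.

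**Working it through.** **1. The plan's own figures.** The inputs are n = 520 per site and a two-sided 5% level (sidedness is not stated, so two-sided is assumed).

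- Widest Wald interval: 2 × 1.96 × √(0.5 × 0.5 / 520) = 0.0860, or 8.6%. This reproduces.
- Power to reject 10% when the true rate is 50%: z = (0.50 − 0.10 − 1.96 × √(0.1 × 0.9 / 520)) / √(0.5 × 0.5 / 520) = (0.400 − 0.0258) / 0.0219 ≈ 17, so power is effectively 100%. This reproduces.

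Both are one-group quantities. The 10% is a benchmark for clinical relevance, not an estimate of attendance without the tool.

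**2. What the article says about the counterfactual.** Statistical Power says that ED referrals to the clinic were rare before the intervention. It gives no rate, the statement is historical, and it covers the ED route only. The clinic's 80% is attendance among patients whom other providers had already referred. It does not say how many flagged patients those providers would have referred.

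**3. Possible size.** The interim Results give 45 uptakes among 339 unique referred patients: 45/339 = 13.3% (the article rounds to about 15%). Assume a background visit probability of 1% to 2%, the same in referred patients; neither is in the article.

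- At 1%: 0.01 × 339 = 3.4 visits; 3.4/45 = 7.5%.
- At 2%: 0.02 × 339 = 6.8 visits; 6.8/45 = 15%.

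The Abstract describes the 45 as scheduled appointments, so this is a share of uptakes, not strictly of completed visits.

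**4. What the threshold contrast could detect.** Statistical Power supposes 40 flagged and 40 similar unflagged patients in each of 12 periods: 12 × 40 = 480 per side. With proportions p1 (flagged) and p0 (unflagged), mean p̄ and n per side:

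power = Φ{ [p1 − p0 − 1.96 √(2p̄(1 − p̄)/n)] / √(p1(1 − p1)/n + p0(1 − p0)/n) }

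The value of p0 is assumed. Adjustment for the risk score costs information; a design effect of 4 is assumed for a linear term with an evenly spread score, so n = 480/4 = 120. The lowest p1 is the crude interim figure 45/1326 = 3.4% (patients scheduled over flagged encounters).

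| Flagged p1 | Unflagged p0 | Power, n = 480 | Power, n = 120 |
|---|---|---|---|
| 50% | 0% to 2% | about 100% | about 100% |
| 10% | 0% | over 99.9% | 95% |
| 10% | 2% | over 99.9% | 75% |
| 3.4% | 0% | 98% | 53% |
| 3.4% | 0.5% | 90% | 37% |
| 3.4% | 1% | 72% | 24% |
| 3.4% | 2% | 27% | 10% |

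At 3.4% against 1% with 480 per side, the difference is 2.4 points (95% CI 0.5 to 4.2). Per site, the contrast is informative at the uptake the plan expected and weak at the uptake seen so far.

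**The case against.** The best defence is that the aim concerns referral from the ED, and that pathway hardly existed before. On that reading the counterfactual is close to zero and a one-group rate is nearly causal. The tool was also updated to exclude patients with a scheduled or completed clinic appointment (Results), which removes some who would have attended anyway. Both points stand, and they are why the bias may be small. They do not settle the matter, because the non-ED route remains open and the article gives no rate for it.

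Three stronger readings are tempting, and the article does not support them.

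- A reader might divide the assumed 1% to 2% by 3.4% uptake per flag (1/3.4 and 2/3.4) and infer that roughly 30% to 60% of counted visits were not caused by the tool. The 45 are counted only among ED-referred patients, so a flagged patient who reached the clinic without an ED referral is not among them. The matching denominator is 339.
- A reader might infer that the needed data are already in hand. The study population includes unflagged patients, and Data Retrieval Process covers risk scores, referral orders and clinic visits, but it does not say that clinic visits are retrieved for unflagged patients.
- A reader might infer that the falls result cannot be interpreted without the jump in visits at the threshold. The falls analysis is intent-to-treat with flagging as the exposure, and that estimate is valid without it. The jump would help only in explaining a null result.

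It is also fair to object that the contrast answers a slightly different question. It estimates the effect of being flagged, whereas the aim speaks of referral, and only (303 + 91)/(1007 + 319) = 394/1326 = 29.7% of flagged encounters led to one. That must be stated, but it matches the exposure that the Discussion itself names.

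**Conclusion.** The mismatch is real and lies in the text: a causal primary question is paired with a one-group estimate, and the threshold comparison is reserved for falls. The planned primary analysis is sound as a description of uptake but cannot show how many visits the tool caused.

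The distortion may be modest: about 7.5% to 15% of the 45 uptakes, if a 1% to 2% background applies equally to referred patients. That background is an assumption. A value near zero would make the problem negligible in practice, and the plan as written could not tell which holds. This is a reason to align the claim with the analysis, not to doubt the completion rates themselves.

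**What to change.** Keep the per-site completion rates and Wald intervals, and label them descriptive. Add a supporting analysis: the flagged versus unflagged contrast at the threshold in any completed mobility and falls clinic visit within 6 months of the index ED visit, from any referral source. Use the same band, date strata and score adjustment as for falls, and apply the appointment exclusion on both sides. State that it estimates the intent-to-treat effect of flagging, and that it was added after interim uptake was known. Base causal statements about completed visits on this contrast alone. If it is not added, reword the aim under Primary Outcome: Completed Referrals as descriptive.

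The cost is one more model and clinic-visit records from the EHR for patients just below the threshold. The estimate is local to the threshold and imprecise per site if uptake per flag stays near 3%, so it should be reported with its interval. Rewording alone costs nothing but gives up the causal claim for the primary outcome.

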#### Secondary Outcome: Return Visits to ED for a Fall

Although the intervention is not randomized, our study has a quasi-experimental design known as a sharp regression discontinuity with regards to intent-to-treat, since the intervention is administered to patients whose risk score falls above some threshold. This design allows for causal inference, provided that differences in outcomes for patients with similar risk scores can be attributed to the intervention (formally, expected potential outcomes are continuous in risk score). This occurs when patients are not manipulating their assignment to the intervention. Assuming this holds, we will primarily analyze only those patients whose risk scores fall within a band around the risk score threshold. Additionally, patients will be stratified by ED arrival date to account for changes to this threshold to be aligned with a sharp research continuity design. A conditional logistic regression model will be built to describe 6-month fall risk at each site as a function of the intervention, patient demographics, and risk score. The odds ratio of a return visit for fall and the 95% CI will be estimated by comparing those identified as high risk by the ML-CDS algorithm and those who were not but had a similar risk profile. Sensitivity analyses will be performed to examine the influence of bandwidth choice and key assumptions (ie, continuity of potential outcomes and linearity in risk score) on estimates. A secondary analysis will be to investigate the effect of covariates on completed referrals and falls using a stratified Cox proportional hazards model for time-to-fall events (right-censored by follow-up time).

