## Methods

### Setting and Patient Population

This study takes place at 3 EDs, described in Table 1, within a health system in the Midwestern United States. All 3 EDs share an instance of the electronic health record (EHR) developed by Epic, though system configuration (eg, nursing flow sheets and order sets) is not identical at the 3 sites.

**Table 1 table1:** Intervention settings.

ED^a^ site	Type	Intervention implementation date	Approximate annual volume of patients, n	Staffing
ED 1	Academic, level 1 trauma center	February 22, 2022	60,000 (25% geriatric)	Attending group 1, advanced practice providers, residents
ED 2	Community	September 27, 2022	22,000 (28% geriatric)	Attending group 1, advanced practice providers
ED 3	Community	Planned September 2023	65,000 (20% geriatric)	Attending group 2, advanced practice providers

^a^ED: emergency department.

The patient population for our study is individuals aged 65 years or older who present to participating EDs between February 22, 2022, and spring 2026, were discharged, and who had (at the time of ED visit) a primary care provider practicing within the health system in which this study is based. Because the ML-based CDS (ML-CDS) will be implemented in a rolling fashion at different EDs within the system, the start date for data will vary at different study sites. Dates were chosen to have at least two years’ worth of index ED data for each site and an additional 6 months of follow-up ED visits to identify subsequent falls.

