## Results

As of April 30, 2023, the CDS tool has been implemented at 2 of the 3 sites. Providers at ED 1 have written 303 referral orders for 260 unique patients, or 5 referrals per week on average, which is our goal. ED 2, the community ED, has not been live with the ML-CDS as long, and providers have written 91 referral orders for 86 different patients, or just over 3 referrals per week. Both EDs refer roughly 30% of patient encounters the algorithm identifies: 303 referrals for 1007 patients flagged at ED 1 and 91 referrals for 319 patients flagged at ED 2. The patient populations between these 2 EDs have substantial overlap, and 6 patients have received referrals from both EDs. After conversations with the mobility and falls clinic, we do not see repeat referrals as a problem unless the patient has already completed 1 of the referrals, so our ML-CDS tool was updated to exclude patients with a completed or scheduled appointment at the mobility and falls clinic. Notably, the patient uptake of the final intervention is about 15% of patients referred—45 patients of 339 unique patients; 1 patient was seen at and referred by both ED 1 and 2—which is less than the 80% that the clinic estimates for other referral sources. While not surprising that uptake would be lower from ED provider referrals than from primary care provider referrals, this conversion rate is lower than we anticipated, and we have taken steps to improve messaging, patient follow-up, and providers’ ability to talk to patients about the program, and we have taken other steps that have shown some improvement appointment conversion in recent months. Additionally, waning concerns about COVID-19 have seemed to increase patients’ willingness to consider completing the referral.

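### The falls effect is planned site by site with no combined estimate; adding one stratified by site and threshold period would answer the programme-level question more precisely

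*Protocol article*

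**What the plan says.** The section on return visits to the ED for a fall plans a regression discontinuity analysis in a band around the risk score threshold: "A conditional logistic regression model will be built to describe 6-month fall risk at each site as a function of the intervention", with demographics and the risk score also in the model. Arrival-date strata deal with the moving threshold: "patients will be stratified by ED arrival date to account for changes to this threshold". Site is not named as a stratum, and no estimate across sites is named.

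The Statistical Power section sizes the falls test on one site's planned accrual, 12 periods of 8 weeks with 40 flagged and 40 unflagged patients each: "Such a test has 89.7% power to detect a difference in fall risk of 10% in a stratified sample size of 12 groups". That figure is given on the condition that covariates are ignored. The one pooled analysis mentioned has another purpose: "We plan on exploratory analysis of pooled data to evaluate the effect of specific covariates on rates of referral".

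The Outcomes section describes the falls outcome as reflecting the overall effectiveness of the intervention, and the Discussion frames the inference as the effect of flagging on future falls. Both are questions about the programme. The Results section adds: "The patient populations between these 2 EDs have substantial overlap, and 6 patients have received referrals from both EDs".

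**The concern.** A programme-level question would be answered by three site odds ratios with no stated way of combining them. If they point in different directions, or all have wide intervals, the reader has no prespecified overall answer. The three estimates would also not be fully independent, because ED 1 and ED 2 share patients.

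The plan already conditions on strata, so adding site to the stratum definition is a small step. It never compares a patient at one ED with a patient at another. At stake is precision on the only outcome that measures falls, and the model needs that precision because it contains the risk score, the variable that determines the flag.

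**Working it through.** **Inputs.**
- Sites: 3 (Setting and Patient Population).
- Per site: 12 periods x 40 = 480 flagged and 480 unflagged; level .05, taken as two-sided; average fall risk 25%; difference 10 points, read as 30% v 20% (Statistical Power).
- Model terms: "as a function of the intervention, patient demographics, and risk score".
- Variance inflation V from adjusting the flag for the score: **not in the documents**. For a linear score, V is 4 if scores are uniform in the band, 3 if triangular and 2.75 if normal. An exponential tail gives about 1.9 to 3.4. A range of 2 to 5 is used.

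**The plan's own figure.** With n per side and no covariates:

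power = Φ[(0.10 − 1.96·s0)/s1], where s0 = √(2 × 0.25 × 0.75/n) and s1 = √((0.30 × 0.70 + 0.20 × 0.80)/n).

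At n = 480, s0 = 0.02795 and s1 = 0.02776, so power = Φ[(0.10 − 0.05478)/0.02776] = Φ(1.63) = 94.8%. The stated 89.7% is lower. That difference is on the cautious side and is not part of this point. On the plan's unadjusted basis, one site has roughly 90-95% power.

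**Standard error, combined against one site.** With information proportional to size, the ratio is √(site size/total size).
- Three equal sites: 1 − 1/√3 = 42%.
- Sites at 5:3:5: 1 − √(5/13) = 38% for the larger sites and 1 − √(3/13) = 52% for the smaller.
- ED 1 and ED 2 only, at the observed flag rates derived below (16.3 and 10.4 per week): 22% for ED 1 and 38% for ED 2.

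**Power and precision with the score in the model.** Multiply s0 and s1 by √V. The 95% half-width is 1.96·s0·√V.

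| V | Power, one site (480 per side) | Power, combined (1440 per side) | Half-width, one site | Half-width, combined |
|---|---|---|---|---|
| 2 | 72% | 99% | 7.7 points | 4.5 points |
| 3 | 54% | 95% | 9.5 points | 5.5 points |
| 4 | 43% | 87% | 11.0 points | 6.3 points |
| 5 | 36% | 79% | 12.3 points | 7.1 points |

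**If site effects truly differ.** Take a between-site SD of 4 points (assumed) and V = 4. One site's standard error is √4 × 0.02795 = 0.0559. The random-effects average has √((0.0559² + 0.04²)/3) = 0.0397, which is 29% smaller. Power is Φ(0.10/0.0397 − 1.96) = 71%, against 43% for one site.

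**If more than 480 per side are available.** Results reports 1007 flags at ED 1 by April 30, 2023, which is 61.7 weeks from launch (16.3 per week), and 319 at ED 2 in 30.7 weeks (10.4 per week). Over 104 weeks these rates give about 1,700 and 1,080 flags. With as many unflagged patients and all of them in the band, single-site power at V = 4 is 92% at ED 1 and 77% at ED 2. If only half count, because of the band and repeat visits, it is 66% and 48%.

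**Smaller effects.** For a 3-point difference (26.5% v 23.5%), combined power is 20% at V = 2.75 and 15% at V = 4.

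**The case against.** Site-level estimation of a secondary outcome is a legitimate choice. The article explains the same choice for the referral model as accounting for variability between sites. The EDs differ in type, volume, attending group and system configuration, and the algorithm is retrained at each. The wording is also not airtight: it speaks of one model and one odds ratio, and the full analysis plan is not shown. All of this stands. It is why the site estimates should remain and the score slopes should be site-specific. It does not supply a combined estimate. The parallel referral analysis builds a model per site, and the falls power is computed on one site's accrual, so the per-site reading is the natural one.

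A reader might go further and infer that each site alone is underpowered, or that pooling restores the stated power. The documents do not support either. The power statement openly sets covariates aside, the loss from score adjustment rests on an assumed V, and the observed flag counts could put single-site power well above the planning-size figures, especially at ED 1.

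Nor is pooling free. A common odds ratio summarises effects that may differ. Shared patients would also enter a single likelihood, so a combined model that ignored repeat patients could overstate its precision.

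**Conclusion.** The point holds as a worthwhile improvement, not as an error that invalidates the plan. The article names no combined falls estimate for a programme-level question, and a more precise one is available from data already being collected.

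The 42% reduction in standard error is exact only for three equal, independent sites with a common effect. Unequal sizes, shared patients or real differences between sites change it. The power gain (72-36% to 99-79%) is conditional on 480 per side, a 10-point effect and V between 2 and 5. It should be quoted as a range with those conditions, not as a deficit the protocol has been shown to have. Combining the sites does little for an effect as small as 3 points. Since falls are the secondary outcome and the planned site results remain valid, the change is advisable rather than essential.

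**What to change.** Before fall outcomes are analysed, add to the plan a combined conditional logistic regression discontinuity estimate across the 3 EDs, with:
- strata defined by site x threshold period;
- the score expressed as distance from the threshold in force at that site;
- site-specific score slopes, because the algorithm is retrained at each site;
- one common flag effect;
- standard errors that account for repeat patients within and across EDs, for example by clustering on patient.

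Keep the site-specific estimates and report a site-by-flag interaction beside them as a check on heterogeneity.

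The cost is analysis-plan wording and some programming, with no new data and no change to the design. The remaining downside is that the combined odds ratio may average over different site effects; the site results and the interaction let the reader see whether it does.
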